#### 6.4 Sample Size

After enumerating the full retrospective cohort, we will randomly select eligible HIV-positive women and their HEIs for our nested cohort. For this nested cohort, our sample size will be determined by a power calculation for our primary outcome of interest—maternal retention in care 12 months after ART initiation. For this calculation (*see summary in Table 2 below*), we assume that 75% of MIPs receive services from a CFL model of interest in our selected districts, and that approximately 73% of HIV-positive mothers receiving the SOC will be retained in care at 12 months post-ART initiation (based on the most recent, first quarter 2017 data from the Malawi national program). With a two-sided alpha of 0.05, we will have 80% power to detect a programmatically meaningful 8% difference in the proportion of mothers retained in care between those who do and do not receive CFL services by enrolling 894 mothers from CFL sites and 298 mothers from SOC sites into our nested cohort (for a total of 1,192 mothers). Assuming that approximately 75% of HIV-positive mothers in SOC sites will be virologically suppressed (a weighted composite of 88% suppression among the 73% of HIV-positive mothers in care and approximately 40% suppression among the 27% of HIV-positive mothers not in care), we will have 83% power to detect a 8% difference in the proportion of HIV-suppressed mothers between those who do and do not receive CFL services. Finally, assuming that we will enrol about one HEI for every mother in the nested cohort, and that 92% of all HEIs not receiving CFL services (i.e. receiving SOC) are alive and HIV-free at 12 months (based on published data that 7% of HEIs become HIV-infected by 12-months and 96% of HIV-exposed but *uninfected* infants are alive at 12 months), we will have 90%

power to detect a 5% difference in HIV-free survival between HEIs who do and do not receive CFL models of interest by recruiting 1,192 total HEIs..

| Table 2: Summary of power and sample size calculations for primary outcomes of interest. |                                 |                    |              |                                 |                                 |
|-------------------------------------------------------------------------------------------------|---------------------------------|--------------------|--------------|---------------------------------|---------------------------------|
| Outcome                                                                                  | Estimated % in SOC sites | Effect Size | Power | Sample Size in CFL Sites | Sample Size in SOC sites |
| Maternal 12-month retention in care                                                             | 73%                             | 8%                 | 0.80         | 894 mothers                     | 298 mothers                     |
| Maternal viral suppression                                                                      | 75%                             | 8%                 | 0.80         | 894 mothers                     | 298 mothers                     |
| Infant 12-month HIV-free survival                                                               | 92%                             | 5%                 | 0.90         | 894 infants                     | 298 infants                     |

For our qualitative and mixed methods study procedures, we have not calculated sample sizes *a priori*, as we will not be conducting statistical hypothesis testing. For IDIs with HIV-positive PMTCT clients, we will select about 60 women across all 5 districts from the approximately 1,200 mother-infant pairs in our nested cohort. For other study activities, we anticipate enrolling the following additional numbers (see section 6.5 below for further details): 1) up to about 8 facility and department in-charges (or designees) and CFL program managers from each of our 20 facility catchment areas to serve as key informants for completing CFL model surveys; 2) about 20 HIV-positive PMTCT clients for private structured observations; 3) a total sample of between about 120 and 240 participants to conduct 30 FGDs with MOH healthcare workers and CFL providers (recruiting a minimum of 4 and maximum of 8 participants per focus group); 4) approximately 10 IDIs with CFL programme site-level supervisors; 5) approximately 5 IDIs with DHMT members (1 per district); and 6) about 5 to 10 IDIs with CFL programme regional/ national managers/ leaders.

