#### **6.4.1 Sampling Approach for Facility Catchment Areas**

Across the 5 study districts, we have identified the characteristics of interest for sampling facility catchment areas to be the district and CFL model (or SOC). To recruit our study population, we will first enumerate all high-volume health facility catchment areas within these districts, where “high volume” is defined as  $\geq 30$  pregnant women newly diagnosed with HIV infection in the catchment area within the last year. We will confirm the CFL model of interest/ SOC active in each facility catchment area prior

to data collection during the study start up phase through consultation with CFL programme managers /directors and District Health Offices (DHOs).

We will then stratify all facility catchment areas according to both district (i.e. 5 districts) *and* CFL model/ SOC (i.e. 4 total models) to create 20 “joint strata”. Within each district, we will randomly select a fixed proportion (ranging between 66% and 100%) of high-volume facility catchment areas to identify approximately **40 facility catchment areas** that will serve as study sites. Table 1 provides an example of our approach to sampling community facility catchment areas within the districts of interest. A minimum of two facility catchment areas (“clusters”) per stratum will be needed to quantify the within and between cluster variability in outcomes of interest (i.e. “rate of homogeneity”), and to provide overall variance and precision estimates. This sampling strategy serves as the starting point for recruiting the study population.

| Table 1: Illustrative sampling approach for study sites.  |                                                                   |                             |                                                             |
|------------------------------------------------------------------|-------------------------------------------------------------------|-----------------------------|-------------------------------------------------------------|
| District                                                  | CFL Model (SOC=0, Mentor Mother=1, Expert client=2, CHW=3) | Joint stratum number | Estimated Number of Sampled Facility Catchment Areas |

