follow-up (LTFU) to the national PMTCT/ART program (defined by the MOH as all those who have not returned to the clinic for more than 2 months after the date when they were expected to run out of antiretrovirals and are not documented as having transferred out, stopped ART, or died); 2) mortality is 30% among HIV-infected mothers who are LTFU; and 3) a coefficient of variation of 0.15 should be adequate to obtain relatively conservative projections of precision in each joint stratum. Applying these considerations to our MIP target population, we will select between 66% and 100% of high-volume sites and about 30 MIPs at each site from across the 20 joint strata to enrol our nested cohort (**Table 3**).

**Table 3:** Illustrative sampling approach for individual mother-infant pairs at facility catchment area level.

| Joint stratum number | Total high-volume catchment areas in strata | Expected catchment areas sampled (66 - 100%) | Expected Range of number of PMTCT mothers available for sampling per joint stratum | Approximate Total Mothers sampled | Approximate Mothers with complete routine care data (.73 SOC, .80 CFLs) | Approximate Mothers Needing Tracing (0.27 SOC, 0.20 CFLs) |
|----------------------|---------------------------------------------|----------------------------------------------|------------------------------------------------------------------------------------|-----------------------------------|-------------------------------------------------------------------------|-----------------------------------------------------------|
| 1*                   | 0                                           | 0                                            | 0                                                                                  | 0                                 | 0                                                                       | 0                                                         |
| 2                    | 0                                           | 0                                            | 0                                                                                  | 0                                 | 0                                                                       | 0                                                         |

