We will explore associations between CFL model and individual-level maternal care retention and infant HIV-free survival at 12 and 24 months using multivariate log binomial regression modelling. We will estimate the effect of receiving any CFL service on the risk of 12-month maternal LTFU and viral suppression, controlling for other measured individual- and catchment area-level covariates, including age, pregnancy number, district, facility type, and number of women registered in the PMTCT cohort, among others; we will conduct a sub-group analysis for women who initiated ART while breastfeeding. We will repeat this analysis to examine effects of CFL model components—including client-to-provider ratio, frequency of provider-client interaction, pro-active versus reactive visit adherence approach, presence of CFL provider remuneration, CFL provider training frequency and duration, availability of one-on-one psychosocial support, and other variables—on maternal 12-month LTFU, maternal viral

suppression, and infant 12- and 24-month HIV-free survival. For maternal viral suppression, we will use survival analysis methods to control for variability in the timing of outcome ascertainment and to enable comparison of viral suppression between groups accounting for interval censoring. For the 24-month HIV-free survival outcome, we will control for infants who do not reach 24 months of age by the time of outcome ascertainment by excluding them from the analysis (so that the outcomes for all infants are represented by those who made it to 24 months in the study). As a check on the robustness of this approach, we will conduct a sensitivity analysis and use inverse probability weighting of those with outcomes at 24 months (compared to the total study sample) to account for any potential differences between infants who have and do not have a 24-month outcome at the time of field outcome ascertainment. Risk differences, unadjusted risk ratios, and adjusted risk ratios with accompanying 95% confidence intervals will be estimated for each model. Of note, these estimates will include the MIPs lost to routine care who are traced through the study, therefore allowing for more robust estimates of true outcomes in the study cohort.

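### The power in section 6.4 and Table 2 carries no design effect, although CFL model is classified by facility and section 6.4.1 itself treats facilities as clusters; section 7.2.2.1 does not carry that cluster variance into the regression

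*Protocol*

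**What the plan says.** Section 6.4 sizes the nested cohort on 12-month maternal retention. It takes it that "approximately 73% of HIV-positive mothers receiving the SOC will be retained in care at 12 months post-ART initiation", and on allocation it says "we assume that 75% of MIPs receive services from a CFL model of interest in our selected districts". With two-sided alpha 0.05 it concludes that "we will have 80% power to detect a programmatically meaningful 8% difference in the proportion of mothers retained in care" with 894 CFL and 298 SOC mothers (1,192 in all). The same counts are credited with 83% power for viral suppression (75% against 83%; Table 2 prints 0.80) and 90% for infant HIV-free survival (92% against 97%). No ICC, design effect or cluster inflation appears in the section or in Table 2.

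Section 6.4.1 describes a clustered design. Catchment areas are stratified by district and by CFL model or SOC, about 40 are selected, and about 30 mothers are sampled at each. It says that at least two areas per stratum "will be needed to quantify the within and between cluster variability in outcomes of interest" and to supply variance and precision estimates.

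Section 7.2.2.1 explores associations between CFL model and "individual-level maternal care retention and infant HIV-free survival at 12 and 24 months using multivariate log binomial regression modelling". It adjusts for individual and catchment-area covariates, weights for facility sampling, pair sampling and participation, and promises 95% confidence intervals. It mentions no cluster-robust variance, GEE or random effect.

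**The concern.** Where exposure is set by facility and outcomes within a facility are correlated, a CFL-against-SOC contrast is informed mainly by differences between facilities. The variance then depends on how many facilities there are as well as how many mothers. Section 6.4.1 recognises this, but the calculation that fixes the sample size does not use it.

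Two things are at stake. If power is well below 80%, a null primary result could be read as no benefit of CFL services when the study was too small to show one. And if the cluster variance foreseen in section 6.4.1 does not reach the regressions in section 7.2.2.1, their intervals would be too narrow.

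**Working it through.** **Inputs.** From section 6.4: p1 = 0.73 (SOC), p2 = 0.81 (CFL), n1 = 298, n2 = 894, two-sided alpha 0.05. From section 6.4.1: about 30 mothers per site. The ICC is not given; 0.01, 0.02 and 0.05 are my assumptions.

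**Reproducing the stated figures (continuity-corrected two-proportion test, independent women).**

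z = (d − c − 1.96 × SE0) / SE1, power = Φ(z), where
- d = 0.81 − 0.73 = 0.08
- c = ½(1/298 + 1/894) = 0.00224
- pooled p = (298 × 0.73 + 894 × 0.81)/1,192 = 0.79
- SE0 = √[0.79 × 0.21 × (1/298 + 1/894)] = 0.02724
- SE1 = √[0.73 × 0.27/298 + 0.81 × 0.19/894] = 0.02887

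z = (0.08 − 0.00224 − 0.05339)/0.02887 = 0.844, so power = 0.801. The same steps give 0.826 for 75% against 83% (text: 83%) and 0.899 for 92% against 97% (text: 90%). The required SOC number for 80% power by this method is 298, exactly the plan's. All three stated powers therefore have a design effect of 1.

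**Adding clustering.** Design effect DE = 1 + (30 − 1) × ICC. It multiplies both variances, so SE0 and SE1 are each multiplied by √DE; c is unchanged. The 298/894 column keeps 30 mothers per site.

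| ICC (assumed) | DE | Power at 298/894 | Power at 180/1,020 |
|---|---|---|---|
| 0 | 1.00 | 0.801 | 0.645 |
| 0.01 | 1.29 | 0.70 | 0.54 |
| 0.02 | 1.58 | 0.62 | 0.47 |
| 0.05 | 2.45 | 0.45 | 0.34 |

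Example, ICC 0.02 at 298/894: √1.58 = 1.257; SE0 = 0.03425, SE1 = 0.03629; z = (0.07776 − 0.06712)/0.03629 = 0.293; power = 0.62. Keeping 80% power at 3:1 would need 4 × 298 × DE, about 1,540, 1,884 and 2,924 mothers.

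**SOC counts in Table 3.** The SOC strata are 5, 9 and 17: 2 + 2 + 2 = 6 sites and 60 + 60 + 60 = 180 mothers. CFL has 1,200 − 180 = 1,020. This is not the 298/894 of section 6.4, and the last column uses it. The fall from 0.801 to 0.645 in the first row is an allocation effect, separate from clustering. The table lists these six as all the high-volume SOC areas, with 80 + 90 + 60 = 230 to 100 + 120 + 100 = 320 women available. Finding 298 SOC mothers in six sites would mean about 50 each, with SOC design effect 1 + 49 × ICC (1.98 at ICC 0.02, against 1.58).

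**If the regression were fitted with no cluster-aware variance.** With exposure constant within facility, the true error of a nominal 5% test is 2 × [1 − Φ(1.96/√DE)]: 0.084, 0.119 and 0.210 at ICC 0.01, 0.02 and 0.05. Correct intervals would be √DE = 1.14, 1.26 and 1.57 times as wide.

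**The case against.** A reader might infer from section 7.2.2.1 that the model treats mothers as independent and that its intervals are too narrow. The protocol does not say so. The section is silent on the variance estimator, while section 6.4.1 says cluster variability will be quantified and used for precision, and the three-part weights belong to a survey-design framework. The choice of estimator is commonly left to a statistical analysis plan, and one may exist that is not shown. This part of the objection stands: the error rates above are conditional.

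It is also tempting to derive an ICC from the statement that "a coefficient of variation of 0.15 should be adequate to obtain relatively conservative projections of precision in each joint stratum". The document does not say what quantity varies, and the statement sits among assumptions for projected weights, so no ICC can be taken from it.

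Exposure may not be wholly constant within a facility. Section 6.5.1.1 allows for more than one model in an area, and section 6.5.2.3.4 collects each woman's own CFL history. To the extent that exposure is analysed per woman, 1 + 29 × ICC overstates the inflation. Adjustment for district and facility type may also lower the residual ICC.

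Finally, Tables 1 and 3 are labelled illustrative, so the six SOC sites are a projection.

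None of this rescues the power statement. It is complete in the protocol, it fixes the sample size, and it contains no allowance for clustering.

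**Conclusion.** The power half holds. The stated 80%, 83% and 90% are figures for independent women and are too high for any positive ICC under the facility-level classification the protocol describes. For retention at 298/894 the power is about 0.70, 0.62 and 0.45 at ICCs of 0.01, 0.02 and 0.05. The size rests on those assumed ICCs, 30 mothers per site and facility-level exposure.

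If recruitment follows illustrative Table 3, the starting point is already about 0.645, falling to about 0.54, 0.47 and 0.34, before any further loss of degrees of freedom from having only six SOC clusters.

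The analysis half holds only as a gap between sections 6.4.1 and 7.2.2.1. Error rates of about 8%, 12% and 21% would follow if no cluster-aware variance were used and exposure were constant within facility. The document does not establish that this is the plan.

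**What to change.** 1. In section 6.4 and Table 2, restate the power, or the detectable difference, with a design effect over a stated range of ICCs. Use the SOC site and mother counts that can actually be achieved, and reconcile them with Table 3.
2. In section 7.2.2.1, state that the CFL-model and component regressions take the facility catchment area as primary sampling unit and the joint stratum as stratum. Specify cluster-robust variance (survey-weighted or GEE) and a small-sample correction based on the number of facilities.

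Both are changes of wording and analysis code; no extra data are needed. The price is wider confidence intervals and a less favourable stated power.

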| 3                    | 0                                           | 0                                            | 0                                                                                  | 0                                 | 0                                                                       | 0                                                         |
| 4                    | 6                                           | 6                                            | 300 - 400                                                                          | 180                               | 144                                                                     | 36                                                        |
| 5*                   | 2                                           | 2                                            | 80 - 100                                                                           | 60                                | 44                                                                      | 16                                                        |
| 6                    | 4                                           | 3                                            | 400 - 500                                                                          | 90                                | 66                                                                      | 24                                                        |
| 7                    | 2                                           | 2                                            | 150 - 200                                                                          | 60                                | 48                                                                      | 12                                                        |
| 8                    | 2                                           | 2                                            | 60 - 100                                                                           | 60                                | 48                                                                      | 12                                                        |

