| 9*                   | 2                                           | 2                                            | 90 - 120                                                                           | 60                                | 44                                                                      | 16                                                        |
| 10                   | 4                                           | 4                                            | 100 - 200                                                                          | 150 #                  | 120                                                                     | 30                                                        |
| 11                   | 2                                           | 2                                            | 300 - 400                                                                          | 90 #                   | 72                                                                      | 18                                                        |
| 12                   | 0                                           | 0                                            | 0                                                                                  | 0                                 | 0                                                                       | 0                                                         |
| 13*                  | 0                                           | 0                                            | 0                                                                                  | 0                                 | 0                                                                       | 0                                                         |
| 14                   | 0                                           | 0                                            | 0                                                                                  | 0                                 | 0                                                                       | 0                                                         |

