| Total         | 45                                   | 40                                    | 2,740 - 3,720                                                               | 1,200                      | 942                                                              | 258                                                |

\*Denotes SOC stratum (see Table 1 above)

#Denotes strata where over-sampling will take place to achieve balance across strata

^Lower estimated number of mothers sampled given highly rural population (see Table 1 above)

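### The stated 80% power rests on 298 SOC mothers, but the sampling plan in Table 3 draws 180; at that number power for the primary outcome is about 0.64

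*Protocol*

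**What the plan says.** Section 6.4 bases the nested-cohort sample size on the primary outcome. Its inputs are:

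- type I error: "With a two-sided alpha of 0.05";
- SOC rate: "approximately 73% of HIV-positive mothers receiving the SOC will be retained in care at 12 months post-ART initiation";
- allocation: "we assume that 75% of MIPs receive services from a CFL model of interest in our selected districts".

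From these it claims "80% power to detect a programmatically meaningful 8% difference in the proportion of mothers retained in care" by "by enrolling 894 mothers from CFL sites and 298 mothers from SOC sites into our nested cohort". Table 2 carries the same 894 and 298 through all three outcomes.

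Table 3 in section 6.4.1 sets out how the nested cohort is to be drawn. An asterisk "Denotes SOC stratum (see Table 1 above"). Five strata carry it: 1, 5, 9, 13 and 17. Strata 1 (Salima) and 13 (Neno) are empty. The Lilongwe row reads "5* | 2 | 2 | 80 - 100 | 60 | 44 | 16" and the Mzimba row "9* | 2 | 2 | 90 - 120 | 60 | 44 | 16". The Zomba row (stratum 17) has the same layout: 2 of 2 catchment areas, 60 to 100 mothers available, 60 sampled. The sampled column totals 1,200 across all strata.

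**The concern.** The power statement and the sampling table describe different designs. The first has a 75:25 split, the second 85:15, and section 6.4 neither mentions the gap nor recomputes power for it.

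The SOC group is the small one, so it limits the powered contrast. Under the protocol's rates, at 180 and 1,020 it supplies 0.73 × 0.27 / 180 = 0.001095 of the variance of the difference, against 0.81 × 0.19 / 1,020 = 0.000151 from the CFL side. That is about 88% of the total, so the extra CFL mothers in Table 3 cannot make up for the missing SOC mothers.

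CFL against SOC is the contrast on which the study is powered and is part of the central hypothesis in section 4.0. If power is near two in three and not four in five, a real 8-point benefit would be missed about one time in three. A null result could then be read as no benefit by people who trust the stated 80%.

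**Working it through.** **Inputs.** Two-sided alpha 0.05. Rates (SOC against CFL): retention 73% against 81%, viral suppression 75% against 83%, infant HIV-free survival 92% against 97% (section 6.4 and Table 2). Group sizes: 298 and 894 from section 6.4; from Table 3, SOC = 60 + 60 + 60 = 180 and CFL = 1,200 − 180 = 1,020. SOC mothers available in Table 3: 80 + 90 + 60 = 230 up to 100 + 120 + 100 = 320.

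**Formula.** The protocol names none. With n1 SOC and n2 CFL mothers, the pooled-variance z test with continuity correction is

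power = Φ[(|p1 − p2| − c − 1.96 × SE0) / SE1], where

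- p̄ = (n1·p1 + n2·p2) / (n1 + n2)
- SE0 = √[p̄(1 − p̄)(1/n1 + 1/n2)]
- SE1 = √[p1(1 − p1)/n1 + p2(1 − p2)/n2]
- c = ½(1/n1 + 1/n2)

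**Step 1: reproduce the stated figure.** At 298 and 894 for retention, p̄ = 0.790, SE0 = 0.02724, SE1 = 0.02887 and c = 0.00224. So (0.08 − 0.00224 − 0.05339) / 0.02887 = 0.844, and power = 0.801. Solved for sample size at 3:1, the same formula returns exactly 298 SOC; without the correction it returns 282. It also gives 0.826 for viral suppression (the text says 83%, though Table 2 prints 0.80) and 0.899 for HIV-free survival (stated 90%). It is therefore very probably the formula that was used.

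**Step 2: put in Table 3's numbers.** At 180 and 1,020 for retention, p̄ = 0.798, SE0 = 0.03246, SE1 = 0.03530 and c = 0.00327. So (0.08 − 0.00327 − 0.06362) / 0.03530 = 0.371, and power = 0.645.

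| Outcome | 298/894, corrected | 180/1,020, corrected | 298/894, uncorrected | 180/1,020, uncorrected |
|---|---|---|---|---|
| Retention | 0.801 | 0.645 | 0.822 | 0.679 |
| Viral suppression | 0.826 | 0.675 | 0.846 | 0.709 |
| HIV-free survival | 0.899 | 0.787 | 0.921 | 0.829 |

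A simulation of the retention comparison at 180 and 1,020 gave 0.642 with the correction and 0.676 without. The retention difference detectable with 80% power becomes 9.5 points (9.2 uncorrected), not 8.

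**Step 3: how far SOC enrolment could rise.** Table 3 already takes 2 of 2 high-volume catchment areas in each SOC stratum, so no further such site is left to add. Reaching 298 needs 298/320 = 93% to 298/230 = 130% of all SOC mothers expected. With CFL at 1,020, continuity-corrected retention power is:

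| SOC mothers | Power |
|---|---|
| 180 (Table 3) | 0.645 |
| 230 (all, low end) | 0.732 |
| 298 (section 6.4) | 0.814 |
| 320 (all, high end) | 0.834 |

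The two full-enrolment rows assume that nobody is lost to refusal, death or missing locator details. If 80% took part (an assumption; the protocol gives no figure), SOC would be 184 to 256 and power about 0.65 to 0.77.

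**Step 4: district adjustment.** Strata 4 (Salima, 180) and 16 (Neno, 90) hold 270 CFL mothers in districts with no SOC site. Section 7.2.2.1 lists district among the covariates. Leaving these mothers out gives 180 and 750, and retention power of 0.618.

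None of these figures allows for clustering by site or for the sampling weights.

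**The case against.** The strongest reply is that Table 3 does not fix the draw. Tables 1 and 3 are both labelled illustrative, the SOC or CFL status of each site is still to be confirmed, and 30 per site is a minimum. Section 6.5.2.3.2 also makes every client a potential participant where the list is shorter than about 50 to 70. The SOC sites average 30 to 60 mothers each (for example 60/2 in stratum 17 and 120/2 in stratum 9), so they would mostly fall under that rule.

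This stands in part. A reader might infer that the study's power is 64%; the documents do not support that as a fixed value. It is the power at the planned 180, which is the low end of the range if each SOC site meets its minimum. But the same section lets selection continue only until at least 30 have enrolled, and does not say that it goes on past 30. Six sites at 30 is 180. The only over-sampling marked in Table 3 is in strata 10 and 11, both CFL.

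Three further limits are fair:

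- The protocol does not name its formula, so for retention the result is better read as 0.64 to 0.68.
- The final estimates also draw on the full retrospective cohort with weighting (section 7.2.2.1). The figures here test the nested-cohort power statement, not that analysis.
- It is tempting to say that the Salima and Neno mothers add nothing. They contribute little to the district-adjusted contrast, but section 7.2.2.1 also plans unadjusted risk ratios, in which they count fully.

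**Conclusion.** The inconsistency is real and lies inside the protocol. Section 6.4 and Table 2 need 298 SOC mothers; Table 3 draws 180. At 180 and 1,020, power is about 0.64 for retention, 0.68 for viral suppression and 0.79 for HIV-free survival by the formula that reproduces the stated values (0.68, 0.71 and 0.83 uncorrected).

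More complete enrolment at the SOC sites would raise retention power to between 0.73 and 0.83. The upper part of that range depends on availability near the top of Table 3's estimate and on almost complete participation. On the protocol's own counts, 298 is out of reach at the low end and needs 93% of everyone at the high end.

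The conclusion rests on Table 3's planning counts, on the rates in section 6.4, and on simple independent samples. It does not show that 80% is unattainable. It shows that the plan as written does not deliver it and does not say so.

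**What to change.** 1. **Restate power.** Rewrite the section 6.4 text and Table 2 for the planned numbers (180 SOC, 1,020 CFL). Name the formula and give power for each outcome over 180 to 320 SOC mothers. Align the viral suppression power in the text (83%) and in Table 2 (0.80) at the same time.
2. **Say what happens at the six SOC sites.** State in sections 6.4.1 and 6.5.2.3.2 that every eligible mother there will be approached and that enrolment will not stop at 30.
3. **Leave the CFL allocation alone.** Taking mothers from CFL strata to hold the total at 1,200 is not recommended. Stratum 19 is 6 sites and 180 mothers, exactly the 30-per-site minimum. Strata 10 and 11 belong to the two smaller CFL models: Table 3 gives mentor mother 300, expert client 330 and CHW 390, and Objective 2 compares these models with each other.

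The cost is a less favourable stated power and some extra work at SOC sites. Full enrolment there adds 230 − 180 = 50 to 320 − 180 = 140 mothers. At Table 3's 0.27 tracing rate for SOC, about 14 to 38 of them would need tracing. The total would rise from 1,200 to at most 1,340. The first step is needed even if the second is adopted, because 298 may still not be reached.
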